### Outcome measures

The primary outcome measures are the gait parameters maximum peak load (in %bodyweight) and step duration (in seconds), which will be analyzed in relation to the discharge date from the rehabilitation center. It is expected that the intervention group will show an improvement in gait parameters and earlier discharge date compared to the control group. The discharge date will be determined by a multidisciplinary team within the usual institutional regime, irrespective of the study protocol. Secondary outcomes include other spatiotemporal gait parameters and validated clinical tests, including the EMS, the FAC, and the VAS. The EMS is a standardized validated scale for assessment of frail elderly people. The FAC is used as a diagnostic and evaluative tool to assess the physical performance of patients. The VAS is a commonly used, subjective scale to assess the amount of pain patients experience. Spatiotemporal gait parameters measured by the SensiStep will be correlated to the clinical test scores (e.g. EMS, FAC, and VAS). Blinding the participants and/or physical therapist is not possible, as both users are aware of the biofeedback they receive in the intervention group. However, data will be encrypted and anonymously delivered by the Steering Committee to the data scientists, which makes the data scientists blinded for the analysis of gathered data.

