This trial is a two-arm, parallel-design, prospective RCT. Based on a previous pilot study, the average length of rehabilitation is 44 days, with a standard deviation of 17. Using a power of 0.80, an alpha of 5%, and an expected reduction of seven days (one week) in two-sided testing, a sample size of 94 participants per group was calculated. Participants will be allocated to either the control group or the intervention group using a stratified cluster randomization according to the sealed opaque envelope principle. First, all rehabilitation clinics were divided into two groups depending on the inclusion rate: < 2 vs. ≥ 2 eligible participants per month. This division was made to avoid skewing of inclusion rate in both arms. Then in both groups, clinics were randomized by the principal investigator into the control or intervention group using the sealed opaque envelope principle. This resulted in six rehabilitation clinics in the control group and five rehabilitation clinics in the intervention group (Table 1). Randomization per center, or cluster randomization, was chosen for two reasons. First, individual selection bias by the physical therapist is minimized. Second, and more importantly, the physical therapists and participants within one center can now provide a single treatment, either care as usual or care as usual, with real-time visual biofeedback. Considering the constant interaction between physical therapists, as well as between participants, individual randomization would increase the risk of data collection errors.

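### The 80% power was calculated for length of rehabilitation, but the declared primary outcomes are two gait parameters, whose power is undetermined

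*Protocol article*

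**What the plan says.** **Sample size (Protocol article, Methods, Study design).** A pilot study is cited, in which "the average length of rehabilitation is 44 days, with a standard deviation of 17". The calculation takes power 0.80, alpha 5% and "an expected reduction of seven days (one week) in two-sided testing", and concludes that "a sample size of 94 participants per group was calculated". No other quantity enters it.

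**Primary outcomes (Methods, Outcome measures).** "The primary outcome measures are the gait parameters maximum peak load (in %bodyweight) and step duration (in seconds". Both are to be analysed in relation to discharge date. The abstract and the closing summary of the Discussion name the same two parameters.

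**Primary analysis (Methods, Statistical analysis).** The primary goal is a relation between the two gait parameters and discharge date. Multiple regression is the method for all relations.

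**Where length of rehabilitation stands.** It is a stated expectation between arms. Outcome measures says "It is expected that the intervention group will show an improvement in gait parameters and earlier discharge date compared to the control group", and the end of the Background hypothesises faster recovery and earlier discharge under biofeedback. It is not in the list of secondary outcomes (other gait parameters, EMS, FAC, VAS). The Protocol subsection has it among additional documented items, beside age and walking aid.

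**The concern.** Three different quantities are in play:

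- the sample size assumes a difference between arms in mean days;
- the named primary outcomes are peak load and step duration;
- the stated primary goal is an association between gait and discharge date.

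Power for one is not power for another. Gait could be associated with discharge date without any treatment effect, and biofeedback could shorten stay by a week without that association appearing.

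The stake is interpretation. A null result on gait could be read against an 80% power claim that never covered it. A clear difference in days, the one result the trial was sized for, would have no listed outcome status. An unseen analysis plan does not settle this, because the article states both the basis of the sample size and the primary outcomes, and they do not match.

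**Working it through.** **1. Reproduce the plan's figure.** Inputs from Study design: difference 7 days, SD 17, two-sided alpha 0.05, power 0.80, equal groups.

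- Standardised difference: 7/17 = 0.412.
- Normal approximation: n = 2 × (1.960 + 0.842)² × 17² / 7² ≈ 92.6, so 93 per group.
- Two-sample t-test: 93.55, so 94 per group. Power at 94 is 0.802 (0.806 by the normal approximation).
- A one-sided test would need 73, which does not fit.

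The stated 94 is therefore the size for one two-sided, two-sample comparison of mean days at 5%, with no allowance for clustering.

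**2. Look for the same inputs for gait.** The article gives no SD, expected difference or target correlation for peak load or step duration. No sample size or power can be computed for them from the document.

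**3. Show the range under assumption.** Assume a simple comparison of two means with 94 per group, individual-level variance and no clustering. With d the assumed difference in SD units, power ≈ Φ(d / √(2/94) − z), where √(2/94) = 0.1459 and z = 1.960 at alpha 0.05 or 2.241 at alpha 0.025 (an even split over two primaries).

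| Assumed gait effect (SD) | Power, alpha 0.05 | Power, alpha 0.025 |
|---|---|---|
| 0.2 | 28% | 19% |
| 0.3 | 54% | 43% |
| 0.4 | 78% | 69% |
| 0.5 | 93% | 88% |

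The effect detectable with 80% power is about 0.41 SD at alpha 0.05 and about 0.45 SD at alpha 0.025.

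**4. The association in the Statistical analysis section.** If this were a single simple correlation over all 188 participants (again an assumption), the value detectable with 80% power at two-sided 5% would be tanh(2.802 / √185) ≈ 0.20. The article gives no target correlation to set beside it.

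**The case against.** The best defence is that discharge date is inside the primary outcome wording, and that earlier discharge under biofeedback is an explicit expectation. The abstract's primary hypothesis also speaks of improved and faster rehabilitation. This stands in part: the powered quantity is tied to the trial's objective, and it would be wrong to say that it appears merely as a covariate for gait. It does not rescue the calculation, because the analysis described is an association, and the difference in days still has no outcome status.

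A reader might go further in two ways that the article does not support.

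- **Inflated type I error.** Two primaries each tested at 5% would give 1 − 0.95² = 9.75%, and adding discharge date would give 1 − 0.95³ = 14.3%. Both figures need independent tests and a rule that any single win counts as success. The article states no such rule, and its Background joins the hypotheses with *and*. If both primaries had to succeed, type I error would not be inflated and the cost would fall on power. Both parameters come from the same 30-m walk, so independence is unlikely. The third test would count a quantity that is not a listed outcome. Alpha allocation may also sit in an analysis plan that is not shown. The 9.75% serves only as an upper bound under an assumed any-win rule.
- **Power cut to a specific figure.** Splitting alpha over two or three tests at 0.41 SD gives about 71% or 66%. That carries an effect size derived from days of stay over to gait, for which the article gives no basis. What is supported is that power for gait is undetermined.

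**Conclusion.** The mismatch holds. The 94 per group and 80% power apply to a between-arm difference in mean length of rehabilitation, and neither to the two declared primary outcomes nor to the stated primary analysis. The sample-size arithmetic itself is correct for its own inputs.

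The size of the problem cannot be fixed as one number. The 28% to 93% range rests on assumed gait effects of 0.2 to 0.5 SD, a two-sample comparison of means, and independent participants. Clinics, not patients, were randomised, so any within-clinic correlation would lower every power figure here, including the 80% for length of rehabilitation. The conclusion does not rest on multiplicity.

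**What to change.** Before any unblinded analysis, align the powered quantity with the primary outcome. There are two valid repairs:

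1. **Make length of rehabilitation confirmatory.** Name its between-arm difference as the primary outcome, with the gait parameters tested after it in fixed sequence or reported as supportive. If it is instead a co-primary beside gait, state the success rule.
2. **Keep gait as primary.** Prespecify a between-arm comparison of peak load and step duration, and give the difference detectable with 94 per group. On the assumptions above this is about 0.41 SD at 5%, or 0.45 SD if alpha is split over two. Converting it to % bodyweight and seconds needs gait SDs that the article does not supply.

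At minimum, restate that the 80% power applies to length of rehabilitation only and that none is claimed for the gait parameters.

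**Cost.** No extra participants are needed to align the text. The first repair costs gait its stand-alone confirmatory status. That is a real loss, because gait is the trial's stated focus and recruitment began in March 2017, so the change must be documented in the protocol and the registry. The second may make the stated power less favourable. The minimum repair is a wording change, but it leaves the declared primaries without a power claim. None of these restores 80% power once clustering is allowed for, since 94 contains no such allowance.

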Therefore, in this randomized controlled trial (RCT), real-time visual biofeedback will be provided to the patient and healthcare professional in the clinical setting by the ambulatory biofeedback system SensiStep (Evalan BV, Amsterdam, The Netherlands). This biofeedback system was previously validated in static and dynamic situations [15]. In short, the system consists of an in-sole force sensor, which is able to measure weight-bearing reliably and continuously during gait. Generated peak loads are directly translated into a LED signal, to provide real-time feedback to the patient. The same signal is sent to a tablet, resulting in a real-time graphical illustration of each step shown to the healthcare professional. By using this biofeedback system, patients can be guided to the optimal level of weight-bearing. This potentially leads to better functional outcome, as well as improved fracture healing through mechanotransduction.

In this RCT, it will be investigated whether elderly patients recover faster or better after proximal femur fractures if they receive real-time visual biofeedback in the clinical setting. The control group receives care as usual and the intervention group receives care as usual with the addition of real-time visual biofeedback to improve weight-bearing to the optimal level. Hypothetically, patients in the intervention group show: (1) an increase in maximum peak loads; and (2) faster step durations at an earlier timepoint in their rehabilitation. Furthermore, patients in the intervention group recover faster, which results in an earlier discharge date.

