## Methods

### Study design

This protocol is described according to the SPIRIT (Standard Protocol Items: Recommendations for Interventional Trials) Statement (see Additional file 1). The study is an international, multicenter trial conducted between March 2017 and August 2018 in the Netherlands and Sweden. Rehabilitation centers focused on geriatric rehabilitation are asked to participate in this study. In order to ensure the quality and expertise of the participating centers, a minimum inclusion rate of at least 20 patients per year is expected. Therefore, the number of eligible patients is screened in each center before their participation in the study. Measurements will be performed by trained physical therapists at the site and all physical therapists are experienced in geriatric trauma care. Before the start of the study, all physical therapists agreed on the study treatment regime during multiple consensus meetings and were trained to uniformly implement this study treatment. Participating geriatric rehabilitation clinics are listed in Table 1.

**Table 1 Tab1:** Participating rehabilitation clinics

Clinic	Place	Allocation (group)
Zorgspectrum *Geinsche Hof* *[name]* *[name]*	Nieuwegein (NL)	Intervention
Warande *Bovenwegen* *[name]* *[name]*	Zeist (NL)	Intervention
Warande *Diakonessenhuis* *[name]* *[name]*	Zeist (NL)	Intervention
Beweging 3.0 *Meander Medical Center* *[name]* *[name]*	Amersfoort (NL)	Control
Evean *[name]* *[name]*	Amsterdam / Zaandam (NL)	Intervention
Beweging 3.0 *Woonzorgcentrum De Pol* *[name]* *[name]*	Nijkerk (NL)	Control
Cordaan *In het Zomerpark* *[name]* *[name]*	Nieuw-Vennep (NL)	Control
azM Herstelzorg *[name]* *[name]*	Maastricht (NL)	Control
Zorggroep Groningen *[name]* *[name]*	Groningen (NL)	Intervention
Careyn *Nieuw Tamarinde* *[name]* *[name]*	Utrecht (NL)	Control
Telge Rehab *[name]* *[name]*	Södertälje (SE)	Control

Participating geriatric rehabilitation clinics in The Netherlands and Sweden. Clinics were allocated to either the control or the intervention group

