### Participants

Strict inclusion criteria will be used to introduce homogeneity of the groups; therefore, participants enrolled in the study meet the following inclusion criteria:The participants rehabilitate from a proximal femur fracture following low energy trauma (e.g. fall from standing position).The participants have a prescribed unrestricted weight-bearing after (surgical) treatment of their fracture.The participants have an expected clinical rehabilitation duration of ≥ 2 weeks.The participants are aged ≥ 60 years.The participants have a bodyweight ≤ 120 kg.

Participants with the following criteria will be excluded from the study:People with cognitive impairment, defined as a score < 18 on the Mini Mental State Examination (MMSE) [16].People who are readmitted to the hospital within two weeks after study participation, for example for infectious complications.People with co-morbidities that affected gait significantly before the proximal femur fracture.

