### Protocol

Data will be gathered according to a strict study protocol (Fig. 1). Candidate patients who fulfill the inclusion criteria will be asked to participate in the study by the site investigator and receive an information letter with the study protocol and study objectives. If patients agree to participate in the study, informed consent will be signed and the cognitive score will be evaluated by the MMSE. The MMSE is an objective score to quantitatively asses the severity of cognitive impairment. A MMSE score < 18 indicates severe cognitive impairment [16] and this leads to exclusion of the patient in this trial. After informed consent and MMSE, data will be collected from participants according to the following trial protocol. The institutional protocol for physical therapy after proximal femur fractures will be followed in all participants. In addition, each participant receives daily force measurements using the SensiStep system in a 30-m walk to measure the gait parameters. Additional clinical tests will be executed to gain additional insight in the rehabilitation progress of each participant:Functional Ambulation Categories (FAC, once per week)Elderly Mobility Scale (EMS, twice per week)Visual Analogue Scale (VAS, daily)

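### The primary gait outcomes are tied to the discharge date, which the intervention is expected to bring forward, so some comparisons this allows can attenuate or mask a gait benefit

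*Protocol article*

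**What the plan says.** - **Outcome.** Under Outcome measures, the primary outcomes are maximum peak load and step duration, "which will be analyzed in relation to the discharge date from the rehabilitation center". Statistical analysis restates the primary goal as finding a relation between these two parameters and discharge date. It names multiple regression as the method and multiple imputation for missing data.
- **Hypotheses.** The gait hypothesis in the Background concerns timing: "faster step durations at an earlier timepoint in their rehabilitation". The discharge hypothesis follows from it: "patients in the intervention group recover faster, which results in an earlier discharge date". Outcome measures repeats both: "It is expected that the intervention group will show an improvement in gait parameters and earlier discharge date compared to the control group".
- **Sizing.** Study design bases the sample size on length of rehabilitation: mean 44 days, SD 17, a 7-day reduction, 94 per group.
- **Measurement.** The Protocol section says "each participant receives daily force measurements using the SensiStep system in a 30-m walk to measure the gait parameters", and Study design adds "Measurements will be performed by trained physical therapists at the site". No fixed assessment day and no post-discharge visit is described. The schedule figure is not available.
- **Discharge decision.** "The discharge date will be determined by a multidisciplinary team within the usual institutional regime, irrespective of the study protocol".
- **Minimum stay.** One inclusion criterion begins "The participants have an expected clinical rehabilitation duration of" and sets this at 2 weeks or more.

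**The concern.** Discharge happens after allocation, and the protocol expects treatment to move it. Used as the reference point for gait, it sets the two hypotheses against each other in three ways.

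1. If patients tend to leave at a similar level of function, gait at discharge looks alike in both arms, even when one arm got there a week sooner.
2. If discharge date enters the regression as a covariate, the model adjusts for something that lies on the path from treatment to outcome.
3. If gait is compared on a later day among those still admitted, both groups are a slower-recovering remainder, and the remainder is more selected in the arm that recovers faster.

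In each case a real acceleration of gait recovery could be reported as a small difference or none, on the outcome named as primary.

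**Working it through.** **1. The protocol's own figure.** Inputs from Study design: difference 7, SD 17, two-sided alpha 5%, power 0.80. The normal approximation gives n = 2(1.960 + 0.842)² × 17² / 7² = 92.6, so 93 per group. The t-test version gives 93.55, so 94. The stated 94 reproduces. It is a figure for length of rehabilitation, not for gait.

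**2. Share discharged by day d.** Assuming normal stays with SD 17 in both arms, the shares are Φ((d − 44)/17) for control and Φ((d − 37)/17) for intervention.

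| Day | Control | Intervention |
|---|---|---|
| 14 | Φ(−1.76) = 3.9% | Φ(−1.35) = 8.8% |
| 21 | Φ(−1.35) = 8.8% | Φ(−0.94) = 17.3% |
| 28 | Φ(−0.94) = 17.3% | Φ(−0.53) = 29.8% |
| 42 | Φ(−0.12) = 45.3% | Φ(0.29) = 61.6% |

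**3. Gait difference among those still admitted.** The protocol gives no gait SD and no correlation between gait and stay. Assume a true gait difference of 7/17 = 0.41 SD and a correlation ρ between better gait and shorter stay. For patients still admitted on day d, the observed difference is

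0.412 − ρ × [φ(b)/Φ(b) − φ(a)/Φ(a)], with a = (44 − d)/17 and b = (37 − d)/17.

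At day 28, a = 0.941 and b = 0.529. The two ratios are 0.310 and 0.494, and the bracket is 0.184. With ρ = 0.5 the result is 0.412 − 0.092 = 0.32. Simulation agrees to two decimals.

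| ρ | Day 14 | Day 28 | Day 44 |
|---|---|---|---|
| 0 | 0.41 | 0.41 | 0.41 |
| 0.3 | 0.38 | 0.36 | 0.32 |
| 0.5 | 0.37 | 0.32 | 0.27 |
| 0.7 | 0.35 | 0.28 | 0.22 |
| 0.9 | 0.33 | 0.25 | 0.16 |

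**4. An illustration in % bodyweight.** Assume log-normal stays (control mean 44, SD 17; intervention stay multiplied by 37/44, so SD 17 × 37/44 = 14.3) and load rising linearly from 50% to 85% at discharge. This is a different stay model from step 2, so the discharged shares above do not apply to it. The all-patient difference depends on what load does after discharge, so both versions are shown.

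| Day | All patients, load keeps rising (cap 100%) | All patients, load held at discharge level | Still admitted only |
|---|---|---|---|
| 14 | 2.4 | 2.4 | 2.3 |
| 28 | 4.4 | 3.2 | 2.1 |
| 42 | 4.4 | 1.8 | 1.3 |

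The held column is also what a last-walk rule would estimate. The difference at discharge is zero here only because every patient is assigned 85% at that point.

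**5. Does the analysis model matter?** In a model where patients leave on reaching a gait threshold, all in-stay daily data were analysed in several ways, with a true slope difference of 0.152 per day.

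- Pooled regression on all daily values: 0.070 (46% of the true value).
- Random-slope mixed model: 0.136 (90%, with some convergence warnings).
- Per-patient slopes: 0.157 (no loss).
- Patient-mean gait: an arm difference of −0.1 unadjusted and −0.6 after adjusting for length of stay, so the benefit does not appear.

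Clustering by clinic is ignored throughout.

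**The case against.** A reader might infer that measurement stops at discharge, that the best walkers leave first, and that the design therefore hides the gait benefit. The documents do not support this as a flat statement.

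- **End of measurement.** On-site daily walks make in-stay measurement likely, but no text says that it ends at discharge, and the schedule figure is not available.
- **Who leaves first.** No gait criterion for discharge is given. The Background makes a link between recovery and discharge plausible but says nothing of its strength. At zero correlation there is no bias.
- **Which analysis.** The protocol names neither an at-discharge arm comparison nor a comparison among remaining inpatients. A fuller protocol or an analysis plan, neither shown, may specify a trajectory model, and step 5 shows that such a model would recover most or all of the effect. Multiple imputation could also help if days after discharge were treated as missing, which the text does not say.
- **Size.** The later-day gaps in step 4 rest partly on load continuing to rise after discharge. With load held, the day-42 gap is 1.8 v 1.3, not 4.4 v 1.3.
- **Other evidence.** Length of admission is recorded and the trial is sized on it, so faster recovery could still show there.

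All of this stands, and it limits the strength of the claim. It does not remove the point. The discharge anchor is stated text, given as the primary goal, and the named method is multiple regression. That is a choice the article has made, not a detail left for later.

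**Conclusion.** The concern holds in conditional form. The primary gait outcomes are anchored to an event after allocation that the protocol expects about 7 days earlier in the intervention arm, and no fixed assessment day is described. If better gait goes with earlier discharge, then an at-discharge comparison, a discharge-adjusted comparison, or a later-day comparison of remaining inpatients can attenuate or mask the benefit.

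The loss is nil at zero correlation. By day 14 it is small unless the correlation is strong. By day 28, between 0.36 and 0.25 of a true 0.41 SD remains for correlations of 0.3 to 0.9, and by day 44 between 0.32 and 0.16. These sizes rest on assumed gait effects, correlations and stay distributions. The direction, towards no difference, follows from the protocol's own hypothesis. The anchor should be changed, with medium confidence about how much the result would be affected.

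**What to change.** - Make the primary gait analysis a between-arm comparison on one prespecified early day, counted from the first SensiStep walk, when few patients are expected to have left. Day 14 is one option, given the expected stay of at least 2 weeks. A somewhat later day such as 21 is also defensible: more patients will have left by then (9% v 17% in step 2), but an effect has longer to develop. The figures do not show that day 14 is best. The criterion concerns expected stay, and the shares in step 2 run on length of rehabilitation, not on this clock.
- For anyone discharged earlier, use the last in-stay walk. In the step 4 illustration this costs almost nothing at day 14 (2.38 v 2.41 points).
- Adjust for days since surgery, since the surgery date is already recorded.
- Alternatively, compare in-stay gait trajectories between arms, through per-patient slopes or a longitudinal model.
- Keep length of stay as a separate arm comparison. Make gait at discharge and the relation between gait and discharge date descriptive.

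The cost is a change of outcome and analysis wording, because the daily walks already supply the data. The downside is that an effect emerging only after the chosen day is left to the descriptive analyses.

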### Interventions

Participants in the intervention group receive, in addition to the standard institutional protocol, real-time visual feedback about weight-bearing during the 30-m walk with SensiStep. The physical therapist has real-time visual insight in the weight-bearing as well by observing the tablet together with the participant. Both the biofeedback system (visually) and the physical therapist (verbally) assist and motivate the participant to adapt the weight-bearing to the optimal level. The target weight will be set at 100% bodyweight, as the participants have no restrictions in weight-bearing.

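### Length of stay, on which the trial is sized, is decided by clinic teams in a single known arm, and no stated analysis separates earlier release from faster recovery

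*Protocol article*

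**What the plan says.** All references are to the protocol article.

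- **Who decides discharge (Outcome measures):** "The discharge date will be determined by a multidisciplinary team within the usual institutional regime, irrespective of the study protocol".
- **Blinding (Outcome measures):** "Blinding the participants and/or physical therapist is not possible, as both users are aware of the biofeedback they receive in the intervention group". The data scientists are the only people said to be blinded.
- **Allocation (Study design, Table 1):** whole clinics are randomized, six to control and five to intervention, and each delivers one treatment.
- **Hypothesis (Background):** "Furthermore, patients in the intervention group recover faster, which results in an earlier discharge date". Outcome measures repeats the expectation of an earlier discharge date.
- **Sample size (Study design):** a pilot study gave a mean stay of 44 days (SD 17), and the target is 94 per arm. The calculation assumes: "Using a power of 0.80, an alpha of 5%, and an expected reduction of seven days (one week) in two-sided testing".
- **Live display (Interventions):** "The physical therapist has real-time visual insight in the weight-bearing as well by observing the tablet together with the participant". This is described for the intervention group.
- **Function (Protocol subsection):** EMS twice a week, FAC once a week and a daily sensor walk, in every participant.
- **Analysis (Statistical analysis):** the primary goal is the relation of peak load and step duration to discharge date. The secondary goal is the relation of gait parameters to the clinical scores. Both use multiple regression.
- **Oversight (Monitoring):** at 30%, 60% and 90% of inclusion the Steering Committee discusses, among other items, the discharge criteria applied to each patient.

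**The concern.** Discharge is a decision, not a measurement. It is taken in a clinic that knows its arm, in a trial whose declared hypothesis is that one arm goes home sooner. Blinding the data scientists protects the analysis, but not an outcome that has already been decided on the ward.

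The hypothesis moves directly from faster recovery to earlier discharge. A shorter stay also arises if teams in intervention clinics release patients at a lower level of function because they expect them to do well. As the stated analyses stand, a positive result on stay could be reported as faster rehabilitation when part or all of it is earlier release. The consequence is not confined to a side outcome: stay is the quantity the trial is powered for, and discharge date also enters the primary gait analysis.

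**Working it through.** **Inputs.** From Study design: SD 17 days, target difference 7 days, two-sided alpha 5%, power 0.80, 94 per group. The size of any expectation-driven shift is not in the documents, so 1, 2 and 3 days are assumed. These are 14%, 29% and 43% of the 7-day target.

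**1. The plan's own figure.** Normal approximation: n = 2 × (1.96 + 0.842)² × 17² / 7² = 92.6, so 93 per group. With the t distribution, 93 per group gives power 0.798 and 94 gives 0.802, so the stated 94 reproduces. This confirms that length of stay is the powered quantity; the arithmetic is not at fault.

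**2. Standard error with independent patients.** SE = 17 × √(2/94) = 2.48 days. A difference of 1.96 × 2.48 = 4.86 days or more is significant.

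**3. False claims under a pure shift.** With no true effect and a shift b, the chance of a significant result favouring the intervention is P(Z > 1.96 − b/2.48).

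| Assumed shift b | b/SE | Chance favouring intervention |
|---|---|---|
| 0 days | 0 | 2.5% |
| 1 day | 0.40 | 6.0% |
| 2 days | 0.81 | 12.4% |
| 3 days | 1.21 | 22.7% |

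A larger sample would not help: SE falls while b stays, so the chance rises.

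**4. Allowing for clustering.** The design effect is not in the documents. With an assumed value of 2, SE = 2.48 × √2 = 3.51 days, and a 3-day shift gives P(Z > 1.96 − 3/3.51) = about 13% instead of 23%. The table is therefore an upper illustration relative to an analysis that allows for clinic. An analysis that ignored clustering that was really present would err in the other direction.

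**5. Would a stated analysis show the shift?** The Statistical analysis section relates gait to discharge date and gait to clinical scores. Neither compares EMS or FAC between arms at discharge, which is where release at a lower level of function would appear. The data for that comparison are already scheduled in both arms.

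**The case against.** The strongest defence has five parts.

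- **The discharge sentence is modest.** A reader might take it as a claim that the decision is blind to arm. Its natural meaning is that the study does not dictate discharge, and the same section admits that participants and therapists cannot be blinded. This stands. The sentence is not false; it simply offers no protection against expectation.
- **There is a safeguard.** A reader might infer that nothing in the plan could reveal the problem. The Monitoring section contradicts that, because applied discharge criteria are discussed patient by patient. This stands in part. The discussion takes place within an interim review described as blinded, sets no common criterion and yields no between-arm result.
- **Function is measured.** A reader might infer that recovery goes unrecorded. It does not: EMS, FAC and daily gait are collected in both arms, and EMS and FAC are secondary outcomes. What is absent is a stated use of them to qualify a difference in stay.
- **The tablet.** It is tempting to say that only intervention therapists see live gait data. The documents do not say so. The live view is described only under the intervention, but every participant is measured with the system, the Background presents the tablet as a general feature, and nothing says it is hidden in control clinics. Also, feedback to the professional is part of the intervention. If it helps a team recognise true readiness sooner, that is an effect of the intervention and not bias.
- **This is a condensed article.** Detailed discharge criteria and analysis specifications may stand elsewhere, and their absence is not criticised here. The point concerns what the article itself fixes: the hypothesis, the powered quantity, who decides it and the stated analysis goals.

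**Conclusion.** The concern holds in a limited form. Stay is decided by clinic teams who work in a single known arm and for whom no blinding is described, and earlier discharge is the stated hypothesis. A shorter stay could partly reflect expectation, and no stated analysis separates that from faster recovery.

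Two premises are inferred. The team's membership and blinding status are not given; lack of blinding follows from clinic-level allocation and from the unblinded therapists. The size of any shift is unknown, and the documents do not show that one will occur. The 6%, 12% and 23% rest on the assumed 1 to 3 days and on a two-arm test of stay that treats patients as independent. The named primary outcomes are gait parameters in relation to discharge date, so stay is the powered and hypothesized quantity but not the sole primary outcome.

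The weakness does not invalidate the design. It limits what a shorter stay can be taken to show, and it can be reduced cheaply.

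**What to change.** Leave discharge decisions with the clinics and make three changes.

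1. **Pre-specify a between-arm comparison of function.** Use the EMS and FAC already scheduled in both arms: the last EMS and FAC before discharge, and the EMS trajectory over days since admission. Allow for clinic in both.
2. **Pre-specify the interpretation.** Call a shorter stay faster rehabilitation only if function at discharge is not worse in the intervention arm, by a margin fixed before outcome data are seen. Otherwise report it as earlier discharge.
3. **State the blinding plainly.** Say that discharge decisions and EMS/FAC ratings are made by staff not blinded to arm, and whether the live display is visible to therapists in control clinics.

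The cost is protocol and analysis wording, with no new assessments. The limits should be stated too. EMS and FAC raters are also unblinded, FAC has only weekly resolution, and scores stop at discharge, the very decision in question. The analysis is therefore supportive and does not remove the bias.
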